### Outcome variables

These will be assessed at enrollment, 6 months, 1 year, 2 years and 3 years after the start of the project. Personnel assessing the outcomes will be blinded to the group of intervention. The primary outcome variable will be change in dmfs count among 1 to 3-year-old children over a follow-up period of three years.

The secondary outcome variables will be:
individual child-level variables: dental caries count (caries reversals and caries increment), S mutans levels, Gingival and Plaque Indexmother and AWW-level variables: oral health-related KAP

Variables that will be measured at baseline and at each of the above time points are shown in Table 1.

**Table 1 Tab1:** Variables to be assessed during the study

Variables Assessment	Variable types	Data Analysis	Anticipated Outcomes	Time of measurement
At the level of the mother (Independent variables)				
Socio-Demographics	Continuous & Categorical	T-test and Chi-square tests.	Assess the distribution of population characteristics	At baseline
Health Literacy Levels	Continuous	T-test	Assess health-related literacy of the individual	At baseline
At the level of the child (Potential Confounders)				
Child Anthropometry (Weight & BMI)	Continuous	T-test	Assess BMI	At baseline and 6 months, 1 year, 2 years and 3-years post-intervention
Oral Health services utilisation	Categorical	Chi-square test	Assess the utilisation of dental care in the last 12 months	At baseline and 6 months, 1 year, 2 years and 3-years post-intervention
At the level of Mother and Anganwadi Worker (Outcomes)				
Oral Health-related KAP	Continuous & Categorical	T-test and Chi-square test	Assess the level of KAP related to oral health issues	At baseline and 6 months, 1 year 2 years and 3-years post-intervention
At the level of Child (Outcomes)				
Dental caries count	Continuous and Categorical	T-test and Chi-square test	Assess the level of dental caries status	At baseline and 6 months, 1 year and 3-years post-intervention
S. mutans levels	Continuous and Categorical	T-test and Chi-square test	Assess the level of dental caries causing organisms	At baseline and 6 months, 1 year and 3-years post-intervention
Gingival and Plaque Index	Continuous and Categorical	T-test and Chi-square test	Assess the level of oral hygiene	At baseline and 6 months, 1 year and 3-years post-intervention

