### Plan for analysis

As the population of children in an AWC is not stable, with older children who cross 6 years of age leaving the AWC and young children joining the AWC; two types of analysis have been planned. The primary analysis will be an inter-group comparison of a stable cohort of children aged 1 to 3 years who will be recruited at the beginning of the study and shall be followed up for 3 years until the age of 4 to 6 years respectively. The secondary analysis will be a cross-sectional inter-group comparison of all available children aged 1 to 6 years present at follow up evaluations (6 months, 1 year, 2 year and 3 years). Children in the secondary analysis will have varying points of entry and different durations of follow-up. All the above-listed outcome variables will be analysed both in the primary and the secondary analysis.

The primary analysis will be done on an intention-to-treat basis. Qualitative data shall be expressed using frequency distribution and percentages, whereas quantitative data shall be expressed as mean (standard deviation) or median (1st, 3rd quartile) depending upon distribution. Normality of distribution will be assessed by Shapiro Wilk test and Q-Q plot. Qualitative variables will be compared between the two groups by chi-square test or Fisher’s exact test, as appropriate. Quantitative variables will be compared between the two groups by Student’s t-test or Mann-Whitney U test, depending upon distribution. Repeated measures analysis between the two groups will be performed using two-way repeated-measures ANOVA or mixed linear models or generalised estimating equations, depending upon the variable and statistical assumptions.

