ECC prevention had conventionally focused upon testing effectiveness of programs targeting behaviour change among the caregivers and children, but surprisingly minimal efforts have had been made to seek translation of these efforts into the reduction of ECC at the community level. The present study shall simultaneously carry with it both the components, i.e. testing effect of altering maternal and child behavioral aspects on ECC incidence through Cohort follow up of 1–3-year-old children for three consecutive years and also a cross-sectional follow up of all available 1–6-year old children at the selected AWCs at regular intervals to look for any change in prevalence of ECC at community level. In other regions of the world surveys of ECC prevalence before and after the intensive educational programs have shown a significant reduction in ECC prevalence [22–27]. A similar decline can be anticipated through this program as well.

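### The cross-sectional secondary analysis is assigned change outcomes (change in dmfs, caries increment, reversals) that some of its children cannot have and that cover unequal periods in the rest

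*Protocol article*

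**What the plan says.** Protocol article, Outcome variables: "The primary outcome variable will be change in dmfs count among 1 to 3-year-old children over a follow-up period of three years". The child-level secondary outcomes begin with "dental caries count (caries reversals and caries increment), S mutans levels". Each of these caries outcomes compares two examinations of the same child.

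Protocol article, Plan for analysis: the AWC population is open, with "older children who cross 6 years of age leaving the AWC and young children joining the AWC". Two analyses follow from that. The primary one follows a fixed cohort recruited at ages 1 to 3. For the other, "The secondary analysis will be a cross-sectional inter-group comparison of all available children aged 1 to 6 years present at follow up evaluations", at 6 months and at 1, 2 and 3 years. The section then states "Children in the secondary analysis will have varying points of entry and different durations of follow-up" and "All the above-listed outcome variables will be analysed both in the primary and the secondary analysis", with no exception for change outcomes.

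The between-group tests named there are the t-test or Mann-Whitney test and the chi-square or Fisher test. A general sentence adds repeated-measures ANOVA, mixed models or GEE but does not tie them to either analysis.

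Protocol article, Discussion: the cross-sectional component exists "at regular intervals to look for any change in prevalence of ECC at community level". The Abstract gives the same purpose. ECC prevalence is not in the outcome list.

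**The concern.** A cross-section of an open population supports outcomes measured at one point in time. It does not support change scores without further rules. A child first examined at a given survey has no change, increment or reversal there. Among children with an earlier examination, the interval depends on when they entered. An average over 1-year and 3-year increments does not estimate the effect over any stated period.

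Caries accumulates with age and time. Each site has one block per arm, so randomisation cannot be relied on to balance age mix or turnover, and children keep joining after allocation. If those patterns differ between the two blocks, the difference can look like an intervention effect or hide one. If they do not differ, the cost is dilution and an unclear estimand.

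Meanwhile the quantity this component is meant to deliver, community ECC prevalence, is not named as an outcome.

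**Working it through.** **The plan's own figure.** Sample size estimation gives mean (SD) 2-year changes of 11 (14.3) and 13.47 (16.3), 5% alpha and 20% beta.

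(1.960 + 0.842)² × (14.3² + 16.3²) / 2.47² = 7.849 × 470.18 / 6.1009 = 604.9, so the stated 605 reproduces. The point does not depend on it; only the mean changes are used below.

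**Inputs from the documents.** Surveys at 0, 0.5, 1, 2 and 3 years (Outcome variables); ages 1 to 6 in the cross-section (Plan for analysis); eligibility from age 0 (Study participants).

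**Assumptions not in the documents.** Ages are uniform; children enter only by ageing in; the first examination is at the next scheduled visit; dmfs accrues linearly.

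**Interval covered by the increment at 3 years**, for ages 1 to under 6 and examination from age 1. A child aged a entered at time 3 − (a − 1).
- Aged 4 to under 6: present at baseline, 3-year interval, 2/5 = 40%.
- Aged 3.5 to under 4: first seen at 6 months, 2.5 years, 10%.
- Aged 3 to under 3.5: first seen at 1 year, 2 years, 10%.
- Aged 2 to under 3: first seen at 2 years, 1 year, 20%.
- Aged 1 to under 2: first seen at this survey, no increment, 20%.

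The shares with no increment at the 6-month, 1-year and 2-year surveys are 10%, 10% and 20%.

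**Effect of pooling.** Accrual per year is 13.47/2 = 6.735 (control) and 11/2 = 5.5 (intervention), a difference of 1.235. Over a full 3 years this is 3 × 1.235 = 3.71 surfaces. Among children with an increment, the mean interval is (0.4×3 + 0.1×2.5 + 0.1×2 + 0.2×1)/0.8 = 1.85/0.8 = 2.31 years, so the difference is 2.3125 × 1.235 = 2.86.

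| Ages | Examined from | 3 y | 2.5 y | 2 y | 1 y | None | Mean interval (y) | Arm difference |
|---|---|---|---|---|---|---|---|---|
| 1 to <6 | age 1 | 40% | 10% | 10% | 20% | 20% | 2.31 | 2.86 |
| 1 to <6 | age 0 | 60% | 10% | 10% | 20% | 0% | 2.45 | 3.03 |
| 1 to <7 | age 1 | 50% | 8.3% | 8.3% | 16.7% | 16.7% | 2.45 | 3.03 |
| 1 to <7 | age 0 | 66.7% | 8.3% | 8.3% | 16.7% | 0% | 2.54 | 3.14 |

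**Without a 2-year caries examination.** Table 1 omits 2 years for caries, although the Outcome variables text includes it. If Table 1 applies, the children in the first row who were first seen at 2 years also lose their increment. The share with none is then 20% + 20% = 40%. The mean interval among the rest is (1.2 + 0.25 + 0.2)/0.6 = 2.75 years, and the arm difference is 2.75 × 1.235 = 3.40. There is less dilution but more children are missing. In the second row the share with none rises from 0% to 20%.

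**The case against.** The best defence is that a workable reading exists. The analysis is called cross-sectional, Table 1 describes the caries outcome as a level of disease status, and the primary outcome is confined to 1–3-year-olds over three years. S mutans, the gingival and plaque indices and KAP are levels and raise no difficulty. Mixed models or GEE can accommodate unequal follow-up, and a condensed article may leave age adjustment to the analysis plan.

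Much of this stands, and it shows that the remedy is small. It does not remove the point. The sentence assigning outcomes makes no exception, and the outcome list spells out increment and reversals. That is a stated rule, not an omitted detail. The models are named only in general terms, and none of them creates an increment for a child examined once.

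Two stronger readings are tempting. A reader might infer that 60% of children at the 3-year survey have no increment, because on the same age assumption 3/5 of them were not yet 1 year old at project baseline. A reader might also infer that the 3-year comparison merely repeats the primary cohort. Both require change to be measured from project baseline. The plan instead says that children enter at different times and have different follow-up, and the outcomes are assessed at enrolment. A later joiner with two examinations therefore has an increment.

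Nor do the documents show that the arms differ in follow-up. Survey dates and the age window are common to both, so bias is a possibility and not a demonstrated fact.

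**Conclusion.** The point holds as a fault in how outcomes are assigned to the secondary analysis. The article places change in dmfs, increment and reversals in a cross-section where a child first examined at the survey has none and the others have increments over different periods. ECC prevalence, the component's stated purpose, is left off the outcome list.

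With a 2-year examination, the illustration gives 0–20% of children without an increment at 3 years and intervals of 1 to 3 years for the rest. The arm difference falls from about 3.7 to about 2.9–3.1 surfaces. Under Table 1's caries schedule, with examination from age 1, about 40% have none and the difference is about 3.4.

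These sizes rest on uniform ages, entry by ageing in only, and linear accrual of another study's 2-year changes. Children who move in and are first seen at a survey would add to those without an increment. The true shares cannot be read from the article. Pooling by itself dilutes and blurs the comparison; it biases it only if entry or age patterns differ between blocks. The primary analysis is unaffected.

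**What to change.** In Plan for analysis, replace the sentence that sends all outcomes to both analyses. Restrict change in dmfs, caries increment and reversals to the 1–3-year cohort. For the cross-section, analyse ECC prevalence and dmfs level at each survey, adjusted or standardised for the child's age, and add ECC prevalence to the outcome list. State which surveys include a caries examination, since Table 1 and the text differ on 2 years.

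The child's age is already among the variables in Measurement of variables. The cost is a few sentences, slightly more analysis work, and no increment result for the open population.

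A split by time since joining, or a separate report of the new intake at 3 years, is optional. The split would need a joining date, which neither Measurement of variables nor Table 1 lists as collected.

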### Sample size estimation

Sample size calculation for the study has been based upon a similar study conducted by Lawrence HP et al., 2008 for prevention of dental caries among aboriginal children in Canada, with 2-year, follow up [18]. In the above study, the mean (SD) change of dmfs in intervention and control arm was 11 (14.3) and 13.47 (16.3), respectively, resulting in a mean difference of 2.47.

Assuming a 5% alpha error and 20% beta error, to detect a mean difference with standard deviations as above, using the sample size formula (z_1-α/2_ + z_1-β_)^2^ x (σ_1_^2^ + σ_2_^2^)/(μ_1_-μ_2_)^2^, the required sample size has been calculated to be approximately 605 in each arm. The design effect due to clustering has not been included, because we do not have prior information about the intra-class correlation within a cluster. To account for an attrition in the number of study subjects, and to account for a decrease in the effect size (due to a potential waning in the performance of AWWs in the intervention clusters over the three-year study period, and a possible Hawthorne effect) it was decided to inflate the sample size approximately 1.5 times, resulting in 950subjects in each arm at each study center (Chandigarh and Cuttack). On average, around 25 children are attached to each AWC. Therefore, at each study centre, a cluster of 40 AWCs will be selected within each of the two ICDS blocks, and the blocks will be randomly located to the intervention and the control arm.

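### The primary analysis is labelled intention-to-treat, but the two-group test tied to the dmfs outcome omits every child without a 3-year examination; one all-visit mixed model should be named instead

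*Protocol article*

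**What the plan says.** The protocol article fixes the outcome under Outcome variables: "The primary outcome variable will be change in dmfs count among 1 to 3-year-old children over a follow-up period of three years". Under Plan for analysis it sets the principle: "The primary analysis will be done on an intention-to-treat basis".

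The methods come from three places:

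- Plan for analysis, general rule: "Quantitative variables will be compared between the two groups by Student’s t-test or Mann-Whitney U test, depending upon distribution".
- Plan for analysis, repeated measures: "two-way repeated-measures ANOVA or mixed linear models or generalised estimating equations, depending upon the variable and statistical assumptions".
- Table 1, row for dental caries count: t-test and chi-square test. No mixed model or GEE is listed there.

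Loss to follow-up is foreseen without a rate. Under Sample size estimation the increase from about 605 to 950 per arm per centre is explained thus: "To account for an attrition in the number of study subjects, and to account for a decrease in the effect size". The second reason refers to waning worker performance and a possible Hawthorne effect.

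The text under Outcome variables schedules assessments at enrolment, 6 months, 1, 2 and 3 years. Table 1 lists the caries count at baseline, 6 months, 1 year and 3 years only.

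**The concern.** Change over three years exists only for a child examined at baseline and again at 3 years. A t-test or Mann-Whitney test on that change is therefore a completers' analysis, whatever its label, and it ignores the interim dmfs of children lost later. Classical two-way repeated-measures ANOVA is stricter: one missed visit removes the child. It is offered alongside mixed models and GEE, which do keep partly followed children, and the choice is left to the type of variable and to assumptions, not to missing visits. The analysed population could thus be settled after the data are seen.

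At stake is bias more than power. If loss is related to earlier caries, and differently in the two arms, the completers' difference is not the difference in the allocated groups. The design gives some reason to guard against this. Only the intervention arm has dentist applications every 3 months, and each arm at each site is a single, geographically separate block, so a local cause of loss falls wholly on one arm.

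**Working it through.** **1. The plan's own figure.** Inputs from Sample size estimation: 5% alpha, 20% beta, SDs 14.3 and 16.3, difference 2.47.

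(1.960 + 0.8416)² × (14.3² + 16.3²) / 2.47² = 7.849 × 470.18 / 6.1009 = 604.9, so the stated 605 is reproduced.

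**2. Ceiling on loss.** 1 − 605/950 = 36.3% (1 − 1/1.5 = 33.3% at exactly 1.5 times). This assigns the whole inflation to attrition, which the document does not do. At this ceiling 605 children per arm remain and nominal power, ignoring clustering, is still 80%.

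**3. Which children each listed method uses.**

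| Method | Children used |
|---|---|
| t-test or Mann-Whitney on 3-year change | those with baseline and 3-year dmfs |
| Two-way repeated-measures ANOVA | those with every visit |
| Likelihood-based mixed model | all with any dmfs; valid if data are missing at random |
| GEE, unweighted | all with any dmfs; needs missing completely at random |

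For ANOVA, with an assumed independent miss rate per follow-up of 10% or 20%: four follow-ups leave 0.9⁴ = 66% or 0.8⁴ = 41% of children. With the three caries follow-ups in Table 1 the figures are 0.9³ = 73% and 0.8³ = 51%.

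**4. Size of completers' bias, by identity.** Let l be the share lost in an arm and g the mean of lost children minus the mean of completers. The completers' mean is the full mean minus l × g, so the bias in control minus intervention is l_I × g_I − l_C × g_C.

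- One-third lost in both arms, equal g: 0.
- One-third lost, g = 3 or 5 dmfs in one arm only: 1.0 or 1.67 in size.
- 10% lost, g = 5 in one arm only: 0.5.

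**5. Simulation.** From the document: 950 per arm, means 11 and 13.47, SDs 14.3 and 16.3. Assumed: normal outcomes, no clustering, all loss after the 2-year visit, correlation 0.8 between 2-year and 3-year change, and log-odds of loss rising by 0.25 or 0.5 per SD of 2-year change. Completers' mean difference (true value 2.47; slope 0.25, then 0.5; 4,000 runs each):

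| Loss | Slope in controls only | Slope in intervention only | Slope in both arms |
|---|---|---|---|
| 36% | 1.27, 0.23 | 3.50, 4.45 | 2.28, 2.20 |
| 20% | 1.82, 1.22 | 3.05, 3.57 | 2.38, 2.32 |
| 10% | 2.13, 1.82 | 2.73, 3.02 | 2.41, 2.37 |

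Repeat runs of the same set-up moved these by up to about 0.1 (for example 1.27 to 1.36). Regressing 3-year change on 2-year change within each arm and averaging over all children, as a stand-in for the mixed model, gave 2.43 to 2.48 throughout. The small bias with equal slopes arises because the two SDs differ.

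**6. Precision with equal slopes.** At 36% loss, empirical standard errors in one set of runs were 0.753 against 0.851 (1 − 0.753/0.851 = 11.5% smaller) and 0.771 against 0.858 (10.1% smaller). The gain falls to about 5% at 20% loss and about 3% at 10%.

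**The case against.** The strongest reply is that the plan already names mixed linear models and GEE, so the remedy is on its own list, and that a journal article may leave missing-data handling to a full protocol or SAP. Much of this stands. A reader might infer that the plan can use only children with complete visits. It does not say so: two of its three repeated-measures options keep partly followed children, and the two-group test needs only the baseline and 3-year examinations.

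A reader might also infer that about a third of the cohort will be lost. No rate is documented, and the inflation also covers a weaker effect. The remark that the Anganwadi population is not stable concerns children entering and leaving the centres. The primary analysis is built on a fixed cohort who are still aged 4 to 6 at the end.

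Nor do the documents show that the effect will be badly biased. The large figures need assumed, arm-specific dropout, and even their direction is open. Referral cards and blinded examinations are described without distinction of arm, so they are no evidence of differential loss. The model's success in the simulation is partly built in, because loss was made to depend on the 2-year value alone, and Table 1 does not list a 2-year caries count.

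What survives is a matter of what the article states, not of what it omits. It links a completers' test to the caries outcome in Table 1 and in its general rule, while calling the primary analysis intention-to-treat.

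**Conclusion.** The point holds as a mismatch between label and method, worth correcting because the correction is nearly free. The test tied to dmfs leaves out every child without a 3-year score, and repeated-measures ANOVA leaves out more.

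The harm is conditional. If loss depends on earlier dmfs in controls only, a true 2.47 is estimated as about 0.2 to 1.4 at 36% loss, 1.2 to 1.8 at 20% and 1.8 to 2.1 at 10%. The same mechanism in the intervention arm alone overstates the effect instead. With a common mechanism the estimate stays between about 2.2 and 2.4, and the benefit of using all visits is mainly precision. These figures rest on the assumed slopes, timing and correlation, and on ignoring clustering; 36% is a ceiling, not a forecast.

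**What to change.** In Plan for analysis, choose from the methods already listed and name one likelihood-based linear mixed model on dmfs at all examinations as the primary analysis. Include every enrolled cohort child in the allocated arm, use visit-by-arm terms, and take the arm difference in change at 3 years as the estimate. Remove the two-group test and two-way repeated-measures ANOVA as primary options for this outcome, and change the caries row of Table 1 to match.

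Reconcile the 2-year caries examination, which is in the text under Outcome variables but absent from Table 1. The model draws on it, and without it less of any dropout bias could be recovered.

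The cost is wording only if the 2-year examination is already intended; no further children are needed. The price is a model-based estimate that relies on data being missing at random, in place of a simple t-test. A delta-adjusted sensitivity analysis and tables of loss by arm and last observed dmfs can be left to the SAP.

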### Plan of study (Fig. 1)

#### Measurement of variables

The following demographic variables and potential confounders will be recorded at enrollment; socio-economic status of children, number of siblings, order and age of children, child anthropometry (weight & BMI), eating patterns, oral health services utilisation by children and health behaviors of children, maternal and child medical history and health literacy levels of mothers etc.

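### The test for the primary dmfs comparison depends on a normality check of the outcome data, so the plan may not estimate the 2.47 mean difference it was sized for, and no stated step uses baseline dmfs, age or site

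*Protocol article*

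**What the plan says.** The Outcome variables section of the protocol article defines the endpoint: "The primary outcome variable will be change in dmfs count among 1 to 3-year-old children over a follow-up period of three years". The Plan for analysis section compares quantitative variables between groups by a t-test or a Mann-Whitney test according to their distribution, and says how the distribution is judged: "Normality of distribution will be assessed by Shapiro Wilk test and Q-Q plot". Table 1 gives dental caries count a t-test and a chi-square test. The same analysis section also names repeated-measures ANOVA, mixed models and GEE, but only for repeated-measures comparisons. The choice among the three is left open and no covariates are named.

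The Measurement of variables section states that "The following demographic variables and potential confounders will be recorded at enrollment" and lists socio-economic status and age among them. The Outcome variables section has outcomes assessed at enrolment, so baseline dmfs is available as well. In Table 1 the variables headed as potential confounders (anthropometry and use of dental services) are given only t-tests or chi-square tests, and both are measured again at each follow-up.

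The Sample size estimation section takes from a cited two-year trial that "the mean (SD) change of dmfs in intervention and control arm was 11 (14.3) and 13.47 (16.3), respectively", "resulting in a mean difference of 2.47", and concludes that "the required sample size has been calculated to be approximately 605 in each arm". The Study design section allocates one cluster of Anganwadi centres (AWCs) to each arm at each of the two sites.

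**The concern.** The trial is sized on a difference in mean dmfs change. A t-test estimates that quantity. A Mann-Whitney test does not: it addresses whether values in one arm tend to exceed those in the other. Its usual companion estimate is a shift, which equals the mean difference only if the two distributions have the same shape. The planning SDs differ between arms, so the protocol's own figures do not describe a pure shift. Letting the outcome data choose the test therefore leaves open what the primary result will measure.

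Neither test, as named, carries a term for baseline dmfs, age or site. Children enter at 1 to 3 years and are followed to 4 to 6 years, so age at entry is likely to matter for how much caries accrues. The article itself describes the two sites as differing in socio-economic background and diet. With very few allocated units, randomisation cannot be relied on to balance such factors. The relevant baseline values are recorded, but no stated analysis of the primary outcome uses them.

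**Working it through.** **1. The plan's sample size.** Inputs from Sample size estimation: SDs 14.3 and 16.3, difference 2.47, two-sided alpha 5%, power 80%.

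n = (1.960 + 0.842)² × (14.3² + 16.3²) / 2.47² = 7.849 × (204.49 + 265.69) / 6.1009 = 604.9, rounded up to 605 per arm.

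The stated figure reproduces. It is a calculation for a difference in means.

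**2. Is skew likely?** SD/mean is 14.3/11 = 1.30 in the intervention arm and 16.3/13.47 = 1.21 in the control arm. If the changes were normal, the share of children with a net fall in dmfs would be Φ(−11/14.3) = Φ(−0.77) ≈ 22% and Φ(−13.47/16.3) = Φ(−0.83) ≈ 20%. Some reversals are expected, since the protocol lists them as a secondary outcome. Net falls in a fifth of children would nevertheless be surprising for a largely cumulative count. Right skew is the more natural reading, but this does not prove it.

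**3. What the normality check would do.** The shape is an assumption: negative binomial counts with the protocol's means and SDs, 1,000 simulated trials per row. A rejection means Shapiro-Wilk p < 0.05 in either arm.

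| n per arm | Shapiro-Wilk rejects | t-test power | Mann-Whitney power |
|---|---|---|---|
| 605 | 100% | 81% | 90% |
| 950 | 100% | 95% | 98% |

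The simulation ignores clustering. A second check used milder skew (gamma data, one sample of 950, 500 runs each). Rejection rates were 21% at skewness 0.1, 60% at 0.2, 91% at 0.28 and 99% at 0.4. Near-certain rejection thus needs some skew, though not much. Under the assumed shape Mann-Whitney loses no power.

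**4. What baseline adjustment could gain.** Set the follow-up SD to 1, the baseline SD to k and the baseline/follow-up correlation to ρ.

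- Change-score variance: 1 + k² − 2ρk
- Baseline-adjusted variance: 1 − ρ²

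The documents give neither k nor ρ. With ρ = 0.5 assumed:

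- k = 1 (equal SDs): 1 + 1 − 1 = 1.00 against 0.75, a saving of 25%.
- k = 0.5: 1 + 0.25 − 0.5 = 0.75 against 0.75, a saving of 0%.

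Because caries accumulates between entry and follow-up, the baseline SD may well be the smaller one, so 25% should not be taken as the expected gain.

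**The case against.** Five counter-arguments deserve weight.

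- **The article never says the comparison is unadjusted.** A reader might infer that covariates are deliberately excluded. The text does not say so, and a covariate list may properly sit in a fuller document. This stands as a limit on wording. It does not remove the point, because the article does state the tests for quantitative outcomes, and those tests carry no covariates.
- **Mixed models and GEE are listed and could carry baseline, age and site.** True. They are offered for repeated measures, as open alternatives, so they do not fix the primary analysis.
- **The switch is not automatic.** A reader might infer that a Shapiro-Wilk p-value alone sends the outcome to Mann-Whitney. The rule also uses a Q-Q plot, and Table 1 names a t-test for caries count, so that reading is too strong. The choice is then a judgement made on outcome data, which is still not pre-specified.
- **Non-normality is not proven.** A change score can be negative, and an SD above the mean does not by itself establish skew. This stands: the 100% rejection depends on the assumed count shape.
- **Adjustment does not cure the allocation problem.** This stands in full. A reader might infer that covariates would protect the estimate from differences between blocks. They reduce measured imbalance only. With one block per arm at each site, unmeasured block effects remain mixed with treatment. Standard errors clustered on AWCs work below the unit of allocation and do not repair that.

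**Conclusion.** The concern holds in a limited form. The stated rule lets the look of the outcome data decide between two tests that answer different questions. If dmfs change is skewed, as the planning figures suggest, the rule points to the test that does not estimate the 2.47 mean difference. Neither named test uses baseline dmfs, age or site, although the first two are recorded and site is known.

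The strength of the pull towards Mann-Whitney rests on an assumed distribution: near certain for negative binomial data at 605 or more per arm, weaker for nearly symmetric data. A reader might infer a loss of power from the switch. The calculations do not support that, since Mann-Whitney did better in the simulated data. The precision gain from adjustment is uncertain, about 0% to 25% of variance at an assumed correlation of 0.5 with baseline SD between half and equal to follow-up SD. The case rests mainly on a fixed, interpretable estimand and on use of measured baseline differences. The limitation from having so few allocated blocks is a separate matter, and this finding does not draw on it for its size. The change is worth making before outcome data are examined.

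**What to change.** - Drop the normality pre-test for the primary outcome.
- Pre-specify one model: three-year dmfs (or three-year increment) on treatment, baseline dmfs, baseline age, socio-economic status and site. Report the adjusted mean difference with a confidence interval from robust standard errors.
- Name a negative binomial model as a sensitivity analysis.
- Use baseline values only as covariates. Anthropometry and service use are also measured during follow-up, when the intervention could have affected them.
- State whether the primary comparison pools the two sites. The site term applies only if it does.
- State separately that, with one block per arm at each site, no child-level model or AWC-level clustering can separate treatment from unmeasured block effects.

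The cost is a change to the analysis text. The covariates named are already collected and no extra participants or visits are needed. Rewording the analysis does not resolve the separate block-level limitation.
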